## Abstract

**Background:**

Patients with moderate to severe acute respiratory distress syndrome (ARDS) exhibit extremely poor prognoses following mechanical ventilation, with mortality rates as high as 40% to 55%. Despite extensive research into ARDS classification and prognostic assessment, the disease’s pathogenesis remains incompletely understood, and there remains a critical lack of specific biomarkers and effective therapeutic targets for its prevention and management. The core challenges lie in two key areas. First, ARDS demonstrates marked heterogeneity in etiology, pathophysiology, and pathogenesis. Existing research, predominantly reliant on population-level average data, fails to capture inter-individual variability, hindering the precise identification of patient subgroups responsive to specific therapeutic regimens. Second, current definitions of ARDS phenotypes are often confined to clinical symptoms and routine diagnostic indices, lacking integrated analysis of deeper mechanistic indicators, such as key biomarkers and respiratory mechanics parameters, thereby limiting the stability and clinical utility of existing classification systems.

**Methods/Design:**

We designed a prospective multicenter cohort study incorporating multi-omics analyses. This research aims to investigate the mechanisms underlying the development and progression of ARDS during mechanical ventilation, providing a theoretical foundation and practical guidance for future ARDS therapies. The study plans to enroll over 165 patients with moderate to severe ARDS receiving mechanical ventilation across 10 medical centers. Peripheral blood and bronchoalveolar lavage fluid (BALF) samples will be collected on the first 24 hours after enrollment and at extubation for metagenomic/meta-transcriptomic sequencing, bulk RNA sequencing, single-cell RNA sequencing, proteomics detection, and metabolomics analyses. Concurrently, comprehensive monitoring of physiological indices, electrical impedance tomography, transpulmonary pressure, pulmonary ultrasound findings, and other relevant parameters will be conducted during the enrollment. Study participants will be stratified by survival and mortality outcomes to analyze the dynamic trends of all measured indices and their underlying molecular mechanisms. Biomarkers derived from multi-omics data and clinical baseline characteristics will be evaluated and integrated, followed by multidimensional dimensionality reduction. Predictive models will be subsequently constructed via early or late fusion to identify core prognostic markers, with performance validated using standardized metrics.

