## Materials and methods

### Purpose of the study

The study aims to identify key risk factors associated with differential survival and mortality outcomes in mechanically ventilated patients with moderate or severe ARDS who exhibit varying prognoses. This objective will be accomplished by investigating the differences and dynamic changes in clinical examinations, respiratory mechanics, lung ultrasound findings, and multi-omics analyses, as well as by further exploring their associations with prognosis. Additionally, the study aims to screen for functionally significant genes and candidate pathways, with a specific focus on lung injury-related mechanistic pathways, and identify the key immune cell subtypes (e.g., alveolar macrophages, T cell subsets, B cells, and myeloid cells) that determine the onset and prognosis of ARDS. Collectively, these efforts aim to provide novel insights and therapeutic targets to advance the precision treatment of ARDS.

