### Data collection

The formal baseline data and serial data of the participants will be collected. Three case report forms (CRFs) have been designed for different stages of patient enrollment management (S2–S4 Files).

The formal baseline data includes the following aspects:

Demographic data: hospitalization number, name, sex, age, main cause of admission, ethnicity, smoking history, and body mass index.

Medical history: hypertension, coronary heart disease, diabetes, kidney disease, hepatopathy, cerebrovascular disease, autoimmunity disease, hemopathy, pulmonary disease, and cancer.

Medication use within 28 days: antibiotics, hormones and immunosuppressants, vasoactive agent, neuromuscular blockers, sedative and analgesic drugs.

Physical examination findings: blood pressure, pulse rate, heart rate, respiratory rate, and temperature.

Severity scores: the Acute Physiology and APACHE II and the SOFA score.

Mechanical ventilation parameters (on day 1 and before extubation): ventilation mode, inhaled oxygen fraction, PEEP, frequency, tidal volume, flow rate, expiratory tidal volume, peak pressure, plateau pressure, airway resistance.

Respiratory mechanics (on day 1 and before extubation): the respiratory system compliance (C_rs_), static compliance of the lungs (C_lung_), respiratory system airway resistance (R_rs_), esophageal pressure (P_es_), transpulmonary pressure (P_tp_), transpulmonary driving pressure (△P_tp_), driving pressure (△P), dead space fraction (V_D_/V_t_) and mechanical power (MP).

Cardiac echocardiography (on day 1 and before extubation): measurement of left ventricular ejection fraction.

Pulmonary ultrasound score and pulse indicator continuous cardiac output parameters.

Serial data: The serial data will be collected on days 1, 3 ± 1, 7 ± 1, 14 ± 2, 21 ± 2, 28 ± 2, and before extubation, discharge or death, including inflammatory markers (white blood cell count, neutrophil count and proportion, interleukin-6, C-reactive protein, procalcitonin, etc.), arterial blood gas, coagulation, blood glucose, blood lipids, electrolytes, myocardial enzymes, immune indicators, BALF tests (cell count, classified examination and etiological examination).

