### Follow‑up schedules

At the 28-day mark, patients will be assessed for the primary outcome of survival or death. At this point, the attending physician will report the primary outcome, and the data collection database will then document the 28-day mortality rate, as well as the duration of ICU and hospital stays, along with other relevant outcomes. During the study period, specific measurements will be taken at predetermined time points: day 1, day 3 ± 1, day 7 ± 1, day 14 ± 2, day 21 ± 2, day 28 ± 2, and before extubation (with priority to day 10 ± 2), discharge or death. The following parameters will be recorded: inflammatory markers, arterial blood gas, coagulation, blood glucose, blood lipids, electrolytes, myocardial enzymes, immune indexes, cell count and classification of BALF and etiological examination. 28-day administration of antibiotics, neuromuscular blockers, vasoactive agent, hormones and immunosuppressants will be tracked. The measurement and collection schedule of this experiment are summarized in the follow-up form (Table 1).

**Table 1 pone.0332985.t001:** The schedule of measurements and visits of this trial.

Timeline (day)	Screening	Follow-up								
	d1	d3 ± 1	d7 ± 1	before extubation (priority: d10 ± 2)	d14 ± 2	d21 ± 2	d28 ± 2	discharged/death (≤28 days)	d1-28	d28
**Informed consent form**	Χ									
**Inclusion/exclusion criteria**	Χ									
**Demographic data**	Χ									
**History of diseases**	Χ									
**ARDS risk factors**	Χ									
**Clinical symptom**	Χ	Χ	Χ	Χ	Χ	Χ	Χ	Χ		
**Imaging**	Χ	Χ	Χ	Χ	Χ	Χ	Χ	Χ		
**APACHE Ⅱ scores**	Χ	Χ	Χ	Χ	Χ	Χ	Χ	Χ		
**SOFA scores**	Χ	Χ	Χ	Χ	Χ	Χ	Χ	Χ		
**mechanical ventilation parameter**	Χ	Χ	Χ	Χ						
**respiratory mechanics**	Χ			Χ						
**pulmonary ultrasound score**	Χ			Χ						
**cardiac echocardiography**	Χ			Χ						
**pulse indicator continuous cardiac output parameters**	Χ			Χ						
**mNGS detection**	Χ									
**Clinical pathogen detection**	Χ	Χ	Χ	Χ	Χ	Χ	Χ	Χ		
**Laboratory examination**	Χ	Χ	Χ	Χ	Χ	Χ	Χ	Χ		
**BALF cell count and classified examination**	Χ			Χ						
**Samples**	Χ			Χ						
**Antibiotic use record**									Χ	
**vasoactive agent use record**									Χ	
**neuromuscular blockers, sedative and analgesic drugs use record**									Χ	
**Adverse events**									Χ	
**28-day survival follow-up**										Χ
**28-day ICU length of stay**										Χ
**28-day ventilator-free days**										Χ

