
### Outcomes

The primary outcome of this study is the 28-day clinical outcome, which includes survival and death. The secondary outcomes include 28-day ICU length of stay and ventilator-free days. For patients with moderate to severe ARDS undergoing invasive mechanical ventilation, additional outcomes include RNA-seq, and scRNA-seq analyses of peripheral blood and BALF will be collected on 24h of inclusion and before extubation. For patients unable to be extubated within 7–14 days, samples will be collected during this period. Respiratory mechanics parameters, severe ultrasound indexes, EIT data, the correlation of physiological parameters will also be evaluated using binary analysis.

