### Statistical analysis

For continuous variables with a normal distribution, the t-test or analysis of variance will be employed to compare means. For those with a non-normal distribution, the rank sum test will be used to compare medians. A Cox regression model will be constructed to establish a predictive model for 28-day mortality in patients with ARDS. The predictive performance of the model will be evaluated using the area under the receiver operating characteristic (ROC) curve, as well as sensitivity and specificity.

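### Grouping by eventual 28-day outcome and comparing serial markers over days 1 to 28 sets ever smaller, selectively depleted groups against each other, so trends can shift without any patient changing.

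*Protocol article*

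**What the plan says.** The abstract (Methods/Design) sets the grouping: "Study participants will be stratified by survival and mortality outcomes to analyze the dynamic trends of all measured indices". The Outcomes section fixes what defines the groups: "The primary outcome of this study is the 28-day clinical outcome, which includes survival and death". Group membership is therefore known only once the 28 days are over.

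The section Purpose of the study makes change over time part of the aim. Risk factors are to be found by "investigating the differences and dynamic changes in clinical examinations, respiratory mechanics, lung ultrasound findings, and multi-omics analyses", and by relating these to prognosis.

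The schedule is in Data collection ("The serial data will be collected on days 1", then 3 ± 1, 7 ± 1, 14 ± 2, 21 ± 2 and 28 ± 2) and again in Follow-up schedules ("specific measurements will be taken at predetermined time points"). A last record is planned as well: "and before extubation, discharge or death, including inflammatory markers". Table 1 applies the full series to laboratory tests, pathogen detection, imaging, symptoms, APACHE II and SOFA. Other indices have only two time points. Respiratory mechanics is listed as "Respiratory mechanics (on day 1 and before extubation", and Table 1 gives lung ultrasound and the biological samples the same two.

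For comparisons of continuous variables, Statistical analysis says that "the t-test or analysis of variance will be employed to compare means", with the rank sum test for non-normal data. It also names a Cox model for predicting 28-day mortality. The text does not say how trends cut short by death or discharge are to be handled.

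**The concern.** The groups are defined by a future event, and that event, or discharge, decides who can still be measured. In the death group each visit loses those who have died since the previous one. In the survivor group each visit loses those who have gone home. The day-14 mean of either group therefore comes from different patients than its day-1 mean.

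If a marker is related to how soon patients die or leave hospital, which is what the study expects of a prognostic marker, the group means drift even when no patient's value moves. A reader would see a falling curve, or two curves converging, and take it for biology. A marker with constant prognostic value could seem to weaken after the first week. Tests that treat the values at a visit as two simple samples cannot reveal this.

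**Working it through.** **Inputs from the protocol (Sample size calculation).** 66 deaths and 28-day mortality of 40%. These reproduce the stated sample size: 66 / 0.40 = 165. The protocol gives no number still under observation at each visit, so there is no stated figure to check for that.

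**Assumed, because the protocol is silent.** The distributions of time to death and time to discharge, and the strength of a marker's relation to each.

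**Step 1: depletion of the death group.** Let S(t) = exp(-λ t^k) with S(28) = 0.60, so λ = -ln(0.60) / 28^k. Among patients who die by day 28, the share still alive at day t is (S(t) - 0.60) / 0.40.

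Example with constant hazard (k = 1) at day 14: S(14) = 0.60^(14/28) = 0.775; (0.775 - 0.60) / 0.40 = 0.436; 66 × 0.436 = 29.

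| Day | k = 0.7 (early deaths) | k = 1 | k = 1.3 |
|---|---|---|---|
| 7 | 37 | 46 | 53 |
| 14 | 22 | 29 | 35 |
| 21 | 10 | 13 | 17 |
| 26 | 3 | 4 | 5 |
| 28 | 0 | 0 | 0 |

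Day 26 is the earliest day in the 28 ± 2 window. Roughly half or more of the death group is gone by day 14 under every shape. These counts are upper limits for the number measured, because they ignore discharge and missed visits.

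**Step 2: effect on the group difference.** Simulated patients each have a marker that is constant over time. The log hazard ratio for death is 0.5 per SD and 28-day mortality is 40%. Time to discharge is exponential, with a mean of 18 days at the average marker value. The table gives the death-minus-survivor difference in mean marker among patients still observed.

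| Discharge assumption | Day 1 | Day 21 |
|---|---|---|
| Log hazard -0.5 per SD, only eventual survivors discharged | 0.56 | -0.03 |
| Log hazard -0.25 per SD, only eventual survivors discharged | – | 0.20 |
| Log hazard -0.5 per SD, eventual deaths can also be discharged | 0.59 | 0.38 |
| Discharge unrelated to the marker | 0.59 | about 0.47 |

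In the first row the intermediate values are 0.36 at day 7 and 0.16 at day 14.

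**Step 3: both curves can move.** With slower discharge (0.03 per day, a mean of 1 / 0.03 = 33 days), log hazards of 0.5 per SD for death and -0.5 for discharge, and only eventual survivors discharged, the death-group mean falls from 0.35 to 0.19 SD between days 1 and 26. The mean of survivors still in hospital rises from -0.23 to +0.12 SD. The gap shrinks from 0.35 + 0.23 = 0.58 to 0.19 - 0.12 = 0.07 SD with no change in any patient.

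**The case against.** The strongest reply is that the protocol nowhere spells out a survivor-versus-death test at each visit. The trend statement is one sentence of the abstract, the tests are listed generically, and a condensed article may leave a longitudinal model to an analysis plan that is not shown. This stands in part: the mere absence of a named longitudinal method would be no finding. What the protocol does state is trend analysis by eventual outcome over a series that death and discharge cut short, and the comparison tests it names do not deal with that.

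A second reply is that a record before discharge or death gives each patient a terminal value, so within-patient change can be studied. This is true and useful. But the timing of that record is set by the outcome, so it does not make groups compared at fixed days comparable.

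A third is reach. The abstract builds the predictive models on multi-omics markers and baseline characteristics, and the primary outcome, the mortality model and the sample size are untouched. This stands and limits the importance of the point.

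Some stronger readings are tempting, and the documents do not support them:
- That both groups lose patients to death: 28-day survivors cannot die before day 28, and they leave by discharge.
- That trends must change by construction: only the composition must; means shift only if the marker relates to the timing of death or discharge.
- That the day-28 death group is empty: the ± 2-day window admits a few late deaths.
- That every index is affected: respiratory mechanics, ultrasound and omics have two time points, where the question is who reaches the second one.

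**Conclusion.** The point holds for the serial laboratory, blood-gas, score and similar data, and should be corrected. The depletion follows from the design. Its pace depends on assumed death times, but under all three shapes about 22-35 of 66 deaths remain at day 14 and only 3-5 at day 26, too few for any useful comparison at the day-28 visit.

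The distortion of the group difference is less certain. For a flat marker under the stated assumptions, the gap shrinks from 0.56-0.59 SD on day 1 to somewhere between 0.47 and -0.03 SD on day 21. The direction was the same in every scenario run, but the size was not. A reader might infer that a marker's signal disappears or reverses through attrition alone. That happens only at the extreme of the range, with discharge strongly tied to the marker and confined to eventual survivors, and the protocol gives no discharge data to support it. Depletion by death alone moves the gap only modestly.

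**What to change.** For the serial markers, base prognostic inference on patients at risk at each time, not on groups defined by what happens later. Either of these would serve:
- a Cox model for death with the marker as a time-updated covariate, and discharge alive handled as a competing event;
- a joint model of the marker trajectory and time to death.

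Keep survivor-versus-death trend plots if wanted, but label them descriptive and print the number observed in each group at each visit. Do not test survivors against deaths at late visits such as day 28, where almost no deaths remain. Limiting the plots to the first week would not remove the problem: in the extreme scenario the gap has already gone from 0.56 to 0.36 SD by day 7.

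The scheduled visits, the record before discharge or death, and the dates of those events supply what is needed, so no new data collection is required. The cost is a change of wording and modest extra programming, more if a joint model is fitted to many markers. Late-visit group differences would no longer be formally tested.

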**Discussion:**

Through comparative analysis of multi-omics data, we aim to identify specific markers and risk factors associated with distinct clinical trajectories of ARDS, further clarifying the key determinants of lung injury. Ultimately, this research will reveal critical immune cell subtypes that govern ARDS onset and prognosis, offering novel insights and therapeutic targets to advance precision medicine for ARDS.

**Study protocol registration:**

ClinicalTrials.gov NCT05922826.

## Introduction

Acute Respiratory Distress Syndrome (ARDS) is a complex clinical syndrome triggered by various risk factors such as pneumonia, infection, trauma, blood transfusion, burns, aspiration, and shock [1,2]. Its core pathological change is increased permeability of the pulmonary vascular endothelium and alveolar epithelium, leading to pulmonary edema and gravity-dependent atelectasis. Characterized by bilateral pulmonary infiltrates and non-cardiogenic pulmonary edema, ARDS presents with progressive respiratory distress and refractory arterial hypoxia [3–6]. Due to the high clinical and biological heterogeneity among patients, there is currently no radical treatment and the global in-hospital mortality rates remaining as high as 40%−55% worldwide [7,8]. Currently proven effective interventions are limited to supportive therapies such as lung-protective mechanical ventilation, prone position ventilation and high positive end-expiratory pressure (PEEP).

Research related to mechanical ventilation has long been the focus of ARDS clinical research. Electrical impedance tomography (EIT) can evaluate the degree of pulmonary collapse in gravity-dependent areas of patients with COVID-19 secondary to ARDS, and the degree of collapse in these areas in the supine position is significantly associated with the improvements in oxygenation during prone positioning [9]. Transpulmonary pressure guided individualized PEEP titration can reduce lung injury and improve prognosis [10]. Critical care ultrasound can real-time monitor ventilation changes during the lung recruitment process through the Lung Ultrasound Score (LUS), facilitating the individualized titration of mechanical ventilation parameters and prognostic evaluation [11–13].

In recent years, the rapid development of molecular biology and bioinformatics has gradually deepened our understanding of the pathophysiology of ARDS. Addressing disease heterogeneity, researchers have used multi-omics technologies such as genomics, transcriptomics, proteomics, metabolomics and metagenomics, to identify subtype-specific therapeutic targets [14–17]. A study on pediatric ARDS identified three transcriptome subtypes (CATS) through cluster analysis of whole blood microarrays, which are respectively associated with pathways related adaptive immunity, complement and G protein-coupled receptor signaling. The mortality of the CATS1 subtype (32%) is significantly higher than that of CATS3 subtype (8%) [18], providing a basis for clinical precise diagnosis and treatment.

Studies on molecular markers have shown that high expression of genes such as *ELAVL-1/HUR* and *GSK3β* is related to the poor therapeutic outcomes in ARDS [19], and high expression levels of p300/CBP in peripheral blood is a risk factor for 28-day mortality [20]. Single nucleotide polymorphisms (SNP) of genes such as *TNF-α* (*rs1800629)*, *IL-6 (rs1800796)*, and *MyD88 (rs7744)* are closely related to the risk of onset and prognosis [21]. The gene expression heterogeneity of alveolar macrophages (AMs) and Peripheral Blood Mononuclear Cells (PBMCs) is significant, and high expression of pro-inflammatory genes in PBMCs often indicates poor outcomes [22]. Down-regulation of genes such as *METTL16* and *FTO* participates in inflammation and lung injury progression by regulating lipopolysaccharide-induced m6A methylation [23].

Proteomic and metabolomic studies have also revealed the characteristics of ARDS subtypes. Analysis of bronchoalveolar lavage fluid (BALF) from ARDS patients shows that the activation of immune response, wound healing, and multiple pathways is more significant in non-survivors [24]. The levels of metabolites such as isoleucine and leucine in BALF, and proline in serum, combined with association with Chronic Health Evaluation (APACHE) II and Sequential Organ Failure Assessment (SOFA) scores, can effectively predict mortality [24,25]. Metagenomic studies have found that changes in the diversity of the lower respiratory tract microecology in ARDS patients are closely related to disease severity and prognosis [26,27], and whole-exome sequencing has identified potential ARDS-related SNP markers [28].

Despite extensive research on ARDS typing, accurate treatment and poor prognosis, the disease progression of ARDS remains unclear, and there are still no specific biomarkers and effective targets for prevention and treatment for ARDS. In the era of precision medicine, integrating multi-demensional information including clinical features, imaging, physiology, biological tests, and multi-omics analyses) to achieve accurate ARDS subtyping is a core research direction for realizing “treatment-feature-matching” and improving the accuracy of therapeutic effect prediction [2,7,8]. This study protocol intends to collect clinical indicators, ventilation parameters, lung ultrasound, and EIT data from multi-center mechanically ventilated patients with moderate to severe ARDS, and integrate multi-omics data including metagenomics, bulked and single-cell transcriptomics, proteomics and metabolomics data from their blood and BALF samples. By summarizing changes in respiratory therapy-related parameters and exploring quantitative indicators for evaluating lung injury, the study protocol aims to identify key factors affecting the occurrence, development, and prognosis of ARDS, providing a basis for precise treatment of the disease.

